## Abstract

**Background:**

The treatment of bipolar disorder (BD) remains a challenge due to the complexity of the disease. Current guidelines represent an effort to assist clinicians in routine practice but have several limitations, particularly concerning long-term treatment. The ARIQUELI (efficacy and tolerability of the combination of lithium or aripiprazole in young bipolar non or partial responders to quetiapine monotherapy) study aims to evaluate two different augmentation strategies for quetiapine nonresponders or partial responders in acute and maintenance phases of BD treatment.

**Methods/Design:**

The ARIQUELI study is a single-site, parallel-group, randomized, outcome assessor-blinded trial. BD I patients according to the DSM-IV-TR, in depressive, manic/hypomanic or mixed episode, aged 18 to 40 years, are eligible. After diagnostic assessments, patients initiated treatment in phase I with quetiapine. Nonresponders or partial responders after 8 weeks are allocated into one of two groups, potentiated with either lithium (0.5 to 0.8 mEq/l) or aripiprazole (10 or 15 mg). Patients will be followed up for 8 weeks in phase I (acute treatment), 6 months in phase II (continuation treatment) and 12 months in phase III (maintenance treatment). Outcome assessors are blinded to the treatment. The primary outcome is the evaluation of changes in mean scores on the CGI-BP-M between baseline and the endpoint at the end of each study phase.

**Discussion:**

The ARIQUELI study is currently in progress, with patients undergoing acute treatment (phase I), potentiation (phase II) and maintenance (phase III). The study will be extended until January 2015. Trials comparing lithium and aripiprazole with potentiate treatment in young BD I nonresponders to quetiapine in monotherapy can provide relevant information on the safety of these drugs in clinical practice. Long-term treatment is an issue of great importance and should be evaluated further through more in-depth studies given that BD is a chronic disease.

**Trial registration:**

ClinicalTrials.gov identifier: NCT01710163

## Background

Bipolar disorder (BD) treatment is a focus of ongoing research to further understanding of the clinical features and possible pathophysiology of the disease. The multivariate factors associated with the etiology of BD, coupled with the variability of clinical presentation, hamper the determination of a specific treatment with optimized outcomes (efficacy and tolerability). Difficulties in BD treatment include delay in diagnosis, high levels of comorbidity, frequent treatment nonadherence and high risk of relapse/recurrence (particularly in the presence of residual symptoms) [1].

Most currently available treatments focus on the acute phase and use a reduction in symptoms ≥50% from baseline as a measure of response. In fact, some responders to treatment continue to experience significant subsyndromic symptoms. A small number of studies have reported remission rates, defined as ≥2 months with no significant signs or symptoms of the disorder [2]. Fewer studies, however, have reported remission during the acute phase through to the maintenance phase of treatment and its predictors [3], which are of great clinical significance. Recent data show that BD treatment under special conditions was associated with full remission in only one-half of the patients and that nearly one-half of the recovered patients relapsed at least once during a 2-year follow up [4]. Maintenance treatment is necessary in BD due to the high mortality, morbidity risk and social and professional impairment associated with poor outcomes [5].

As monotherapy, quetiapine has proven more effective than lithium in the treatment of depression at doses ranging from 150 to 600 mg [6,7], with no significant difference found between 300 and 600 mg doses [8]. The drug has also shown similar efficacy in the treatment of mania at doses of between 600 and 800 mg compared with lithium after 4 weeks and with haloperidol after 84 days [9-11], although response in mania was slower when compared with haloperidol [11]. To date, quetiapine is the only antipsychotic medication with evidence of efficacy across all phases of bipolar disorder [7], and was recently indicated as the first choice in monotherapy for the treatment of bipolar depression [12,13].

On the other hand, lithium is the first-line choice for the maintenance treatment of BD, particularly for classic (euphoric) mania and bipolar depression, according to many open controlled studies, with additional clinical effects such as antisuicidal properties, augmentation and treatment of acute unipolar depression and recurrent depression [14]. Some studies have shown lithium to be more specific for manic and less effective for depressive episodes [15] while an accumulating body of evidence tends to support its specificity in psychiatric usage, particularly in patients with classic BD.

In Brazil, lithium is the first treatment choice in all BD phases, representing a suitable and affordable treatment option. However, treatment under the Brazilian Public Health System (Sistema Único de Saúde) has financial limitations, where atypical antipsychotics and some anticonvulsants are currently not made available for use in BD. Few controlled studies on the most-used treatments for the general population are therefore conducted compared with trials involving the latter medications, which the pharmaceutical industry has an interest in promoting [16].

Aripiprazole is an atypical antipsychotic with a single mechanism of action that shows partial agonist activity at dopamine D_2_ and D_3_ and serotonin 5-HT_1A_ receptors, as well as antagonist activity at serotonin 5-HT_2A_ receptors [17,18]. The drug is US Food and Drug Administration approved for the treatment of mania and maintenance of BD 1, and has proven effective in several trials for the adjunctive treatment of bipolar depression and major depressive disorder [19-22].

Despite the drug’s proven efficacy in the treatment of manic episodes [23], results of aripiprazole monotherapy in bipolar depression have been poor, with benefits not persisting beyond 8 weeks [24]. Some data, albeit not robust, suggest the drug’s efficacy as an adjunct for potentializing treatment in bipolar I depression, although it is unclear whether this response persists beyond the acute phase [25].

Information in the general literature regarding augmentation of treatments initially refractory in trials, as well as on the combination of atypical antipsychotics in acute and maintenance phases, remains scarce.

## Methods/Design

### The ARIQUELI project

The ARIQUELI (efficacy and tolerability of the combination of lithium or aripiprazole in young bipolar non or partial responders to quetiapine monotherapy) study is a randomized trial designed to assess the add-on therapies of lithium or aripiprazole for augmentation of quetiapine treatment.

### Design of the ARIQUELI study

The two key elements of the ARIQUELI project were based on the rationale described above. For the first element, the disorder was considered as a whole; that is, patients with different clinical presentations (such as depression, mania or mixed episodes) shall receive the same treatment. The treatment focus is relapse/recurrence prevention as opposed to treating a particular phase. Patients are to undergo long-term follow-up given that BD is a chronic and recurrent disorder. The second key point is that comparing the augmentation strategy using lithium versus aripiprazole should help clarify the role of atypical antipsychotic drugs in the treatment of BD.

This is a single-site, parallel-group, randomized, outcome assessor-blinded trial. The study protocol was reviewed and approved by the appropriate institutional review board in accordance with the standards and guidelines established in the current amendment of the Declaration of Helsinki, and consistent with good clinical practice and applicable regulatory requirements. Written informed consent was obtained from all patients prior to any study-related activities. Methodological details of all phases of the ARIQUELI study have been presented in accordance with the Consolidated Standard of Reporting Trials 2010 Statement [26].

The local institutional review board approved the study (Hospital das Clinicas Ethical Committee, CAPPESQ #26436). All subjects and/or family members provided written informed consent before entry into the study.

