### Sample size and randomization

Sample size was calculated by comparing the mean difference in Clinical Global Impression for Bipolar Disorders (CGI-BP-M) scores between baseline and endpoint for the two groups. Comparison using Student's *t* test showed that a sample of 50 patients (25 in each group) attains an 80% power (at 5% significance level) for detecting a difference of 0.8 standard deviations, considered a large effect size [27]. Owing to the exploratory nature of this study and the difficulties regarding compliance in long-term trials, this was deemed an acceptable value [27].

The random allocation sequence was computer generated by a biostatistician. Patients were enrolled by clinicians who have their code revealed by the research monitor when assigned to interventions. Blinding of outcome assessors is ensured by keeping their evaluations independent from those of the clinicians.

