### Planned analyses

The primary analysis will entail evaluation of mean scores on the CGI-BP-M between baseline and endpoint in both groups. In addition, differences shall be evaluated by comparing the two treatment groups according to the total number of patients in full remission at the study endpoint and the reason for and timing of drop out. Continuous data will be represented as mean and standard deviation whereas categorical variables will be described by a table of frequencies. The results of all statistical comparisons of the treatment groups will be expressed as two-sided *P* values rounded to three decimal places. The criterion for statistical significance in all comparisons will be *P* ≤0.05.

Continuous variables will be compared using repeated-measures of analysis of variance, with the treatment group and study phase as factors. Rates of response, remission and dropouts will be compared between the two groups using Pearson's chi-square test for categorical data. Dichotomous measures will also be compared using odds ratios and 95% confidence limits.

The correlation of clinical issues, quality of life, social adjustment and cognitive impairment will be evaluated by Pearson's correlation.

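### The stated CGI-BP-M model omits episode polarity, a plausible prognostic factor; prespecifying it as a covariate would recover some precision at almost no cost

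*Protocol article*

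**What the plan says.** Under Eligibility, the protocol article admits bipolar I patients in any current episode type and gives no quota or expected mix. Under Design of the ARIQUELI study, pooling is a stated principle: "patients with different clinical presentations (such as depression, mania or mixed episodes) shall receive the same treatment". The reason given is that the trial aims at preventing relapse, not at treating one phase of illness.

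Planned analyses fixes the model: "Continuous variables will be compared using repeated-measures of analysis of variance, with the treatment group and study phase as factors". Polarity is not among the factors, and no result by polarity is mentioned. On allocation, Sample size and randomization says only: "The random allocation sequence was computer generated by a biostatistician".

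The Background gives reasons to expect response to vary with polarity. On lithium: "Some studies have shown lithium to be more specific for manic and less effective for depressive episodes". On aripiprazole, after noting proven efficacy in mania: "results of aripiprazole monotherapy in bipolar depression have been poor, with benefits not persisting beyond 8 weeks". The same section also contains evidence pointing the other way. Lithium is described as first-line maintenance treatment in both mania and bipolar depression. Aripiprazole as an adjunct is reported to have worked in several trials in bipolar depression, with later wording that calls the bipolar I data suggestive but not strong.

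**The concern.** Giving every patient the same treatment regardless of polarity does not require comparing the arms as if polarity were uninformative. Primary outcomes defines the endpoint as change in CGI-BP-M at the end of each phase, and Study phases sets the potentiation phase at 8 weeks. Over that interval the current polarity may well bear on the score change. Secondary outcomes adds that the scale has separate mania, depression and global parts, so patients of different polarity start high on different parts of it.

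If polarity predicts change and is left out of the model, its variation stays in the error term, and any chance difference in polarity between two arms of 25 stays in the observed treatment difference. What is at stake is precision in a small trial, and how far a reader can interpret a pooled estimate that has no breakdown by polarity.

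**Working it through.** **Inputs from the article.** Sample size and randomization gives N = 50 in two arms of 25, with 80% power at the 5% level. The target is 0.8 SD, which the article regards as large. Planned analyses makes the tests two-sided and names treatment group and study phase as the model factors.

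**Inputs assumed.** The article gives neither the polarity mix nor the effect of polarity on outcome. I use two polarity groups, a share of 50-70% for the larger one, and a prognostic gap *g* (difference in mean change between polarities, in SD units) of 0.25 to 0.8.

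**1. The article's own figure.** The noncentrality is 0.8 × √(25/2) = 2.83. Two-sided 5% power at 25 per arm is 80.7% by the normal approximation and 79.1% by the exact noncentral t (48 df). The stated 80% is reproduced.

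**2. Chance imbalance if allocation is simple.** The SD of the between-arm difference in polarity share is √(2p(1−p)/25), which is 0.141 at p = 0.5 and 0.130 at p = 0.7. The exact binomial probability of a gap of at least 5 patients out of 25 (20 points) is:

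| Share | Probability |
|---|---|
| 50% | 0.203 |
| 60% | 0.193 |
| 70% | 0.164 |

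Conditioning on the overall polarity split (hypergeometric) gives 0.26 at 50% and 0.22 at 70%.

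**3. Effect on the realised difference.** Shift = imbalance × *g*.

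| *g* (SD) | Shift at a 20-point imbalance (SD) | Share of the 0.8 SD target |
|---|---|---|
| 0.25 | 0.20 × 0.25 = 0.05 | 6% |
| 0.5 | 0.20 × 0.5 = 0.10 | 12.5% |
| 0.8 | 0.20 × 0.8 = 0.16 | 20% |

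The standard error of the unadjusted difference is √(2/25) = 0.283 SD, so the largest of these shifts is 0.16/0.283 = 0.57 standard errors.

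**4. Gain from adjustment.** With equal shares and total SD 1, polarity explains R² = 0.25*g*², the residual SD is √(1−R²), and the error df are 47. Power for 0.8 SD at N = 50:

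| *g* (SD) | R² | Power |
|---|---|---|
| unadjusted | – | 79.1% |
| 0.25 | 0.016 | 79.7% |
| 0.5 | 0.063 | 81.6% |
| 0.8 | 0.160 | 85.6% |

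No extra patients are needed.

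**5. What a breakdown by polarity can show.** With half the patients in each group, the standard error of the arm difference within one polarity is √(2/12.5) = 0.40 SD, so its 95% interval is about ±1.96 × 0.40 = ±0.78 SD. The interaction contrast has standard error √(2/12.5 + 2/12.5) = 0.566 SD. A test of it has about 29% power for an interaction of 0.8 SD (25% at a 30:70 split), and 81% (74%) for 1.6 SD. These estimates can only be descriptive.

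**The case against.** The strongest reply is that pooling is declared and justified, that the article calls the study exploratory, and that extra covariates and subgroup descriptions are usually left to an analysis plan that is not shown. The justification covers how patients are treated. It does not explain why a likely predictor should be absent from the comparison. The article also does not leave the model open: it names the factors. The point therefore stands, but as a refinement and not as an error or a contradiction.

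Three stronger readings are tempting, and the document does not support them.

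- *Allocation ignored polarity.* A reader might infer this from the brief description of the sequence. The article is silent on stratification, which a condensed article commonly leaves to the full protocol. The imbalance probabilities above are conditional on simple allocation.
- *The arm comparison is biased.* Under randomisation, chance imbalance has zero expected effect and does not inflate type I error. The unadjusted standard error already contains it. It can distort one realised estimate, and it costs precision.
- *The article itself says the two add-ons perform differently by pole, so the pooled result depends on case mix.* The poor aripiprazole result is for monotherapy, whereas the trial tests augmentation, and the Background also reports favourable evidence for both drugs in depression. Where it reports weakness in depression, it does so for both drugs, in the same direction. That makes polarity plausibly prognostic. It does not show that the lithium-aripiprazole contrast varies. If the contrast is the same in each polarity, the pooled effect does not depend on the mix. If it were, say, 0.8 SD in mania and 0 in depression, the pooled effect would be 0.24, 0.40 or 0.56 SD at 30%, 50% or 70% mania. That is a possibility, not a finding.

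One practical objection also stands. Allocation follows 8 weeks of quetiapine, or a new episode of any polarity in phase III, so polarity at randomisation may differ from that at entry, and both scales may be raised. A classification rule is needed.

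**Conclusion.** The point holds in a limited form. The stated CGI-BP-M model leaves out a plausible prognostic factor that can be obtained from scales already collected. If allocation is simple and the larger polarity group makes up 50-70% of patients, an imbalance of 20 points or more has a probability of about 16-20%, and it would shift the realised difference by 0.05-0.16 SD for prognostic gaps of 0.25-0.8 SD. Adjustment would move exact-t power from 79.1% to between 79.7% and 85.6%: negligible if polarity predicts weakly, useful if it predicts strongly. The polarity mix and the prognostic gaps are assumptions, because the article gives neither. The sample size is not in question, and neither is the decision to treat all polarities alike.

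**What to change.** Prespecify polarity at randomisation as a covariate in the CGI-BP-M model, with a written rule that classifies each patient from the Hamilton and Young Mania scores at the time of allocation, including patients in whom both are raised. Because the outcome is change, polarity must act on the change itself; if the model is fitted to scores across phases, this means including polarity by phase. Report the lithium-aripiprazole difference by polarity, with confidence intervals and labelled descriptive, beside the pooled estimate, which remains the primary result. If the full protocol already stratifies by polarity, the same term belongs in the model for that reason.

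The cost is one degree of freedom in each comparison of change for a two-level factor (two if mixed episodes are kept separate), one table, and subgroup estimates that will be imprecise. No additional patients or assessments are needed, and because the article describes the trial as still in progress, the change can be made before the analysis.

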### Interventions

After diagnostic assessments, the patients initiate treatment with quetiapine for 8 weeks as described above. For acute treatment, patients shall receive a starting dosage of 100 mg on day 1, to be increased by 100 mg/day to 300 mg on day 3. The 300 mg dose shall be subsequently adjusted until reaching the most effective dose according to clinical criteria. The patient dose shall be determined according to individual tolerability, and a maximum dose of 800 mg will be allowed for this study. Patients showing remission or >50% reduction in baseline scores on the Hamilton Depression Scale and the Young Mania Rating Scale shall proceed to the maintenance phase for a further 18 months. Patients showing score reductions <50% on the scales will be allocated to one of the arms of the augmentation phase. Group I will receive lithium at the standard dose: starting at 300 mg daily, the weekly dose will be adjusted according to blood serum level (between 0.5 and 0.8 mEq/l) according to efficacy and tolerability. Group II will receive aripiprazole: starting at 10 mg daily, the dose will be adjusted up to 15 mg daily according to efficacy and tolerability. The only concomitant medications permitted are lorazepam at doses of 0.5 to 4 mg/day and biperiden at 2 to 8 mg/day.

### Eligibility

Patients are recruited from within the Institute of Psychiatry, Clinicas Hospital of the University of Sao Paulo School of Medicine. BD I patients according to DSM-IV-TR [2], in depressive, manic/hypomanic or mixed episode, aged 18 to 40 years, are eligible for the study. To be included, patients must score at least 8 points on the Hamilton Depression Scale or 10 points on the Young Mania Rating Scale. Patients with comorbid conditions are allowed to participate due to the real clinical study approach (‘more likely naturalistic study’). Patients in previous use of quetiapine and lithium or quetiapine and aripiprazole combinations will not be included. Other exclusion criteria include presenting with schizophrenia, mental retardation (IQ <90) or unstable clinical conditions.

Eligible patients currently under pharmacological treatments have to undergo a washout period according to the medication in use: 1 week for antidepressants, antipsychotics, lithium, valproate, carbamazepine and other anticonvulsants; 2 weeks for irreversible MAOI; and 4 weeks for fluoxetine and clozapine.

### Sample size and randomization

Sample size was calculated by comparing the mean difference in Clinical Global Impression for Bipolar Disorders (CGI-BP-M) scores between baseline and endpoint for the two groups. Comparison using Student's *t* test showed that a sample of 50 patients (25 in each group) attains an 80% power (at 5% significance level) for detecting a difference of 0.8 standard deviations, considered a large effect size [27]. Owing to the exploratory nature of this study and the difficulties regarding compliance in long-term trials, this was deemed an acceptable value [27].

The random allocation sequence was computer generated by a biostatistician. Patients were enrolled by clinicians who have their code revealed by the research monitor when assigned to interventions. Blinding of outcome assessors is ensured by keeping their evaluations independent from those of the clinicians.

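### The 80% power assumes all 50 patients are evaluable: no allowance for loss is made, it cannot carry over to phase III, and no confidence interval is stated for the primary outcome

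*Protocol article*

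**What the plan says.** Sample size and randomization bases the size on a Student's t test of CGI-BP-M change between the two augmentation groups. It concludes that "a sample of 50 patients (25 in each group) attains an 80% power (at 5% significance level". The target is 0.8 SD, which the article itself describes as large. It names no phase, gives no dropout rate, and does not say whether the 50 are randomised or evaluable. It defends the choice in one sentence: "Owing to the exploratory nature of this study and the difficulties regarding compliance in long-term trials, this was deemed an acceptable value".

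Study phases takes follow-up to 2 years, admits only responders to phase III, and removes from the study those without response after phase II. Primary outcomes places the CGI-BP-M evaluation at the end of every phase.

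Planned analyses makes the P value the form in which every group comparison is given: "The results of all statistical comparisons of the treatment groups will be expressed as two-sided". It adds means and standard deviations for continuous data, and odds ratios with 95% confidence limits for dichotomous measures. It mentions no interval for a difference in means.

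**The concern.** One power figure is given for a primary outcome measured at several time points, and it leaves no room for missing patients. Loss of patients normally leads either to more randomised patients or to a lower stated power. Here compliance difficulty is a reason for accepting the value, and the 80% is left unchanged.

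Randomisation follows phase I, so the randomised comparison exists only at the ends of phases II and III. By the end of phase III, the design itself has removed patients according to their response. A reader who applies the 80% to the long-term comparison, which Design of the ARIQUELI study presents as the focus, would be misled about what the trial can detect.

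The reporting plan adds to this. The trial is sized for a large difference between two active add-ons. A P value above 0.05 does not by itself show which differences remain compatible with the data, and an interval would.

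**Working it through.** **Inputs.** From Sample size and randomization: n = 25 per group, difference d = 0.8 SD, 5% level, Student's t test, power 80%. From Planned analyses: two-sided testing. Loss rates are assumptions, because the documents give none.

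**Reproducing the stated figure.** The noncentrality is d × √(n/2) = 0.8 × √12.5 = 2.83.
- Normal approximation: power = Φ(2.83 − 1.96) = 80.7%. Required n = 2 × (1.960 + 0.842)² / 0.8² = 24.5, so 25 per group.
- Exact (noncentral t, 48 degrees of freedom): power = 79.1%. Required n = 25.52, so 26 per group for a full 80%.

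The two results lie on either side of 80%, so the figure reproduces. There is no reserve: 24 evaluable per group gives 77.4%.

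**Power with loss.** This takes 50 randomised, equal loss in both groups and a t test on those remaining. Evaluable n per group = 25 × (1 − loss), and power comes from the noncentral t with 2n − 2 degrees of freedom. The 95% confidence interval half-width, in SD units, is t(0.975; 2n − 2) × √(2/n). A half patient per group stands for an odd total. In those rows the detectable difference is given for the whole numbers on either side.

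| Assumed loss | Evaluable per group | Power for 0.8 SD | Difference detectable with 80% power | 95% CI half-width |
|---|---|---|---|---|
| 0% | 25 | 79.1% | 0.81 SD | 0.57 SD |
| 10% | 22.5 | 74.6% | 0.84 to 0.86 SD | 0.60 SD |
| 20% | 20 | 69.3% | 0.91 SD | 0.64 SD |
| 30% | 17.5 | 63.2% | 0.96 to 0.99 SD | 0.69 SD |
| 40% | 15 | 56.2% | 1.06 SD | 0.75 SD |

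**Which time points are affected.**
- End of phase II: the removal rule acts after this assessment, so it takes no one out of this comparison. Only ordinary dropout matters.
- End of phase III: those who did not respond in phase II have left, and dropout up to 2 years comes on top. If 50 are randomised, 25 evaluable per group requires every one of them to respond and to stay.

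**Reporting.** Setting the sentences of Planned analyses side by side, dichotomous measures get an estimate with 95% limits. Continuous measures get group means, SDs and a P value. CGI-BP-M change, the primary outcome, falls in the second group. Even with all 50 evaluable, an observed difference of zero would leave differences up to 0.57 SD in either direction inside the interval.

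**The case against.** **A reader might infer that the 80% is an arithmetic error**, because the exact test gives 79.1% and asks for 26 per group. It is not. The gap is under one percentage point, and the normal approximation gives exactly 25.

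**A reader might infer that only P values will be reported.** The documents do not support that, since means, SDs and odds ratios with confidence limits are planned. Group means, SDs and numbers would also allow an approximate unadjusted interval. What remains is narrower: the section assigns intervals to one type of outcome and not to the type that includes the primary outcome. It could be said that an article leaves this to the analysis plan. But the article does fix how comparisons are expressed, and it states limits for dichotomous measures only.

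**A reader might infer that the removal of phase II non-responders weakens the phase II comparison.** It does not, because they leave after that assessment.

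**Every loss rate used here is assumed.** The remark on compliance is general and is not a forecast of dropout. If 50 means evaluable patients, the shortfall disappears, but the text does not say so. The planned repeated-measures analysis may also have different power from a t test on those remaining. These points make the size conditional. They do not supply an allowance for loss.

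**The article is open about its limits.** It calls the study exploratory and the effect large. That lowers the seriousness, but it does not tell the reader which time point the 80% refers to.

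Nothing in the article plans a claim of equivalence, and it gives no expected difference between the add-ons. Neither a misuse of a non-significant result nor a likely non-significant result can be read from it.

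**Conclusion.** The concern holds in a limited form. The 80% is correct to rounding, on condition that all 25 per group are evaluable. No allowance for loss accompanies it, although compliance difficulty is acknowledged in the same paragraph.

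If 50 is the number randomised, the stated power cannot apply at the end of phase III unless every patient responds and stays. At the end of phase II it applies only without dropout. Under assumed losses of 10% to 40%, power for 0.8 SD falls from about 75% to 56%. The detectable difference is 0.91 SD at 20% loss and 1.06 SD at 40%. These sizes rest on equal loss in both groups and a two-sided t test on the remaining patients.

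Separately, no confidence interval is stated for the between-group difference in the continuous primary outcome. Both matters should be corrected. Neither invalidates the design.

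**What to change.** In Sample size and randomization:
- Say whether 50 is the number randomised or the number evaluable.
- Tie the 80% to the end of phase II with all 50 evaluable. The Abstract and Study phases give this phase different lengths (6 months and 8 weeks), and these must be reconciled so that the time point is clear.
- Give the power under a range of losses labelled as assumptions, for example 75%, 69%, 63% and 56% at 10%, 20%, 30% and 40%.
- State that the phase III comparison does not have the stated power.

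In Planned analyses, report the between-group mean difference in CGI-BP-M change with its 95% confidence interval alongside the P value.

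This costs wording and a little analysis work, and no patients are added. The only downside is a less favourable stated power. For scale, keeping 25 evaluable per group would instead mean randomising 25 / 0.8 = 31.25, so 32 per group, at 20% loss, and 25 / 0.6 = 41.7, so 42 per group, at 40%. That is not proposed here.
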